### Participant timeline

The participant timeline is seen in Table 4.

**Table 4 tab4:** Participant timeline.

Event	Day 1	Months											
		1	2	3	4	5	6 months follow-up	7	8	9	10	11	12 months follow-up
Assessment for eligibility	*X*												
Acceptance of enrolment	*X*												
Randomization/allocation	*X*												
Questionnaire	*X*						*X*						*X*
Reminder of treatment allocation	*X*	*X*	*X*	*X*	*X*	*X*	*X*			*X*			*X*
Possibility to contact staff of trial	*X*	*X*	*X*	*X*	*X*	*X*	*X*	*X*	*X*	*X*	*X*	*X*	*X*

LAMA, long-acting muscarinic antagonist.

Every electronic mail to the participants will include a direct hyperlink to a FAQ on https://coptrin.dk/, and an e-mail that they can contact in case of further questions.

### Sample size

In Denmark, approximately 400,000 people are assumed to have COPD; however, approximately a quarter of them have not been diagnosed yet. We have data showing that 178,000 citizens have collected LAMA medication within the last 6 months. At the same time, we know that every year, there are approximately 20,000 admissions with AECOPD (severe AECOPD) and 6,000 deaths in patients with COPD. Assuming 50% of the AECOPD admissions are either unique or preceding a death, there are 16,000 annual events corresponding to our primary outcome. Thus, the annual risk of a primary outcome is approx. 16,000/178,000 = 8.9%. We hypothesize that evening LAMA administration will reduce the relative risk of the primary outcome by 25%, corresponding to a 2.2% absolute risk reduction. Assuming 84.4% uniformly distributed adherence to the intervention (= approximately 1 in 6 does not adhere), this corresponds to a relative risk reduction of 21.3% = 1.9% absolute risk reduction (average effect among all) in the ITT population. Alpha and power (1-beta) are set at 0.05 (two-sided) and 0.8, respectively. This leads to a needed sample size of 6,662 (3,331 + 3,331).

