**Results:**

A total of 10,013 participants were randomized, and the recruitment process started on 9 March 2023. Secondary outcomes include (i) moderate COPD exacerbations; (ii) all-cause hospitalization; (iii) ICU admission; (iv) need for non-invasive ventilation; and (v) all-cause mortality, among others. All outcomes will be evaluated 12 months after recruitment.

**Clinical trial registration:**ClinicalTrials.gov, NCT05563675.

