## Assignment of interventions: allocation

### Sequence generation

Patients will be randomized 1:1 to one of the two treatment strategies by computer-generated allocation to either LAMA administration in the morning or evening.

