### Interim analyses and stopping guidance

A Data and Safety Monitoring Board (DSMB) will be appointed and act according to a charter agreed by the investigators and approved by the sponsor. Six months after the recruitment of the last patient, an interim analysis, based on the ITT population, will be performed to evaluate the continuation of the trial. As main statistical measures, an O’Brien-Fleming plot of the primary endpoint and mortality (calculating *Z*-scores) will be performed. The interim analysis will be performed and presented by a sub-investigator not otherwise involved in the data collection or analyses, overlooked by the trial statistician. The data will be presented in a blinded fashion.

At the interim analysis, the event rate and effect size for the primary endpoint, as well as the safety and progress of the study, will be assessed by the DSMB, and follow-up duration may be adjusted accordingly. Safety will be assessed by comparing event rates to the event rate presumption used for the initial sample size determination. The study may stop for futility if it is deemed improbable to achieve a follow-up duration sufficient to detect a clinically important effect size. The study will not stop for superior efficacy at interim analysis. We wish to prioritize increasing the likelihood of having sufficient power to conclude on the secondary endpoints at the final analysis.

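### The 8.9% planning risk is not like-for-like, with a net error that cannot be derived from the article, and as an annual figure it is a poor benchmark for interim safety

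*Protocol article*

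**What the plan says.** Protocol article, Sample size. The annual events come from "approximately 20,000 admissions with AECOPD (severe AECOPD) and 6,000 deaths in patients with COPD". Half of the admissions plus all of the deaths gives 16,000. The section then states: "Thus, the annual risk of a primary outcome is approx. 16,000/178,000 = 8.9" (per cent). The denominator is described as "178,000 citizens have collected LAMA medication within the last 6 months". On the wider population, the same section says that "approximately 400,000 people are assumed to have COPD; however, approximately a quarter of them have not been diagnosed yet". The resulting sample size is 6,662, while the abstract's Results paragraph reports: "A total of 10,013 participants were randomized".

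The planning figure is used again under Interim analyses and stopping guidance: "Safety will be assessed by comparing event rates to the event rate presumption used for the initial sample size determination". That analysis takes place six months after the last patient is recruited. The same section plans Z-scores for the primary endpoint and mortality, and asks the DSMB to look at event rate and effect size. Adverse event reporting and harms is marked as not applicable.

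**The concern.** A risk is meaningful only if its events and its people belong to the same group. Here the events come from all admissions for AECOPD and all deaths in COPD, and the people are LAMA collectors. About 300,000 of the 400,000 people with COPD are diagnosed, so at least 300,000 − 178,000 = 122,000 diagnosed patients can add events without being in the denominator. Taken alone, that makes the risk too high.

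Two things depend on the figure. One is the power statement, by which a neutral result will be interpreted. The other is interim safety. An annual rate is a lenient yardstick for participants followed for less than a year, and it stands outside the randomised comparison. An excess of events in the evening arm could pass unremarked if that sentence were applied as written.

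**Working it through.** **Inputs.** From Sample size: 16,000 events, 178,000 collectors, 300,000 diagnosed, 25% relative risk reduction (RRR), 84.4% adherence; "Alpha and power (1-beta) are set at 0.05 (two-sided) and 0.8, respectively". Allocation is 1:1 (Sequence generation). From the abstract: 10,013 randomised, taken as 5,006 per arm.

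**1. Reproducing the plan's figure.** p1 = 16,000/178,000 = 0.0899. RRR = 0.25 × 0.844 = 0.211. p2 = 0.0899 × 0.789 = 0.0709. d = p1 − p2 = 0.0190, and p̄ is the mean of p1 and p2.

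n0 = [1.960√(2p̄(1−p̄)) + 0.842√(p1(1−p1) + p2(1−p2))]² / d² = 3,226 per arm.

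With continuity correction, n = (n0/4)[1 + √(1 + 4/(n0·d))]² = 3,331 per arm, or 6,662 in total. This is the stated number exactly, so the arithmetic after the 8.9% input is sound. (The printed 8.9% and 21.3% should read 9.0% and 21.1%; neither slip affects the sample size.)

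**2. Which way the input errs.** Let s be the share of the 16,000 events that fall in LAMA users with COPD, f the share of collectors who have COPD, and e the additional events from emergency room visits as a fraction of s × 16,000. The like-for-like risk is 8.99% × s(1+e)/f. The article gives none of the three. With e = 0 and s = 0.8 assumed:

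| f | Risk | Power at 6,662 |
|---|---|---|
| 1.0 | 7.2% | 70% |
| 0.8 | 9.0% | 80% |
| 0.7 | 10.3% | 86% |

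The sign therefore depends on unknown quantities. Any e above zero raises the risk further.

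**3. Sensitivity of power.** Power = Φ{[d − 1/n − 1.960√(2p̄(1−p̄)/n)] / √([p1(1−p1) + p2(1−p2)]/n)}, with RRR held at 21.1%:

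| Control risk | Where it comes from | Power at 6,662 | Power at 10,013 |
|---|---|---|---|
| 9.0% | the plan | 80% | 93% |
| 6.7% | assumed: f = 1, s = 0.75 | 67% | 84% |
| 6.1% | solved for 80% at 10,013 | 62% | 80% |
| 5.3% | 16,000/300,000 | 55% | 74% |

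**4. The safety benchmark.** Suppose 8.99% is right, the hazard is constant, and there are 5,006 per arm.

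- *Six months for everyone (the shortest case).* Control risk = 1 − √(1 − 0.0899) = 4.6%. At relative risk 1.5 the evening arm shows 6.9%. Z = (0.0690 − 0.0460)/√(2 × 0.0575 × 0.9425/5,006) = 4.9. The arm stays under 8.99% up to a relative risk of 0.0899/0.0460 = 1.95.
- *Nine months for everyone.* Control risk = 1 − (1 − 0.0899)^0.75 = 6.8%. Relative risk 1.5 gives 10.2%, which exceeds the benchmark. Relative risk 1.3 gives 8.9% (0.0887), just under it, with Z = 3.8.
- *Full 12 months, but true control risk 5.3%.* The arm stays under the benchmark up to 0.0899/0.0533 = 1.69. Relative risk 1.5 gives 8.0% with Z = 5.4.

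The first two cases need no error in the planning risk, only follow-up shorter than the benchmark's twelve months.

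**The case against.** A reader might infer that 8.9% is an upper bound and that the stated power is therefore overstated. The article does not support either. The 178,000 are collectors of a drug, whereas Eligibility criteria separately requires a confirmed COPD diagnosis; collectors without COPD dilute the denominator. Table 1 counts emergency room visits, which the numerator omits. LAMA users may also be at higher risk than the average diagnosed patient, so 5.3% is a sensitivity value and not a corrected one. Dividing by all 400,000 would be worse, since that includes undiagnosed people who cannot be enrolled.

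The number randomised also absorbs much of any shortfall. At the planning risk the trial has more power than stated, and about 80% remains down to a risk of 6.1%. Recruitment is complete, and the relative risk will be reported with its confidence interval whatever the planned power was. All of this stands, and it reduces the power part to a matter of honest description.

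On safety, a reader might infer that the DSMB would see no between-arm data. That is not so: Z-scores for the primary endpoint and mortality are planned, and effect size is to be assessed. A relative risk of 1.5 would show up there. A harm rule, or scaling for follow-up, may also be in the DSMB charter, which is not shown. What remains is that the article's one sentence on how safety is judged points to the external annual rate and not to those Z-scores.

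**Conclusion.** The concern holds in a limited form. The planning risk does not describe the trial population, and the document cannot show whether it is too high or too low. Power for the 10,013 randomised runs from 93% at 9.0% to 74% at 5.3%, given an RRR of 21.1%; these are illustrations, not estimates.

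The safety sentence is the weightier part. With six months of follow-up for all and a constant hazard, a 50% excess of events lies below the benchmark (6.9% against 8.9%) even if the planning risk is exactly right. Six months is the extreme, because earlier recruits will have been followed for longer and the article does not give the mix. The nine-month case shows that the blind spot narrows as follow-up lengthens.

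**What to change.** **Sample size.** Re-derive the control risk from registry events among LAMA users with COPD, using the Table 1 definition. If that cannot be done, label 8.9% an assumption. In either case state power for the 10,013 randomised over a sensitivity range such as the one above. Do not call 8.9% an upper bound or present 4.0% (16,000/400,000) as a planning value.

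**Interim analyses and stopping guidance.** Replace the safety sentence with a between-arm comparison of the primary endpoint and mortality, using the planned Z-scores against a harm boundary set in advance in the charter. Keep the presumed event rate, scaled to the follow-up accrued, only for judging power and follow-up duration.

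**Cost.** Text changes to two sections and to the charter, plus one registry tabulation if the risk is re-derived. No further recruitment is needed, and the between-arm Z-scores are already planned. The power statement may look better or worse than 80%, depending on the risk found.

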### Recruitment

Through the Danish Health Data Authority, COP:TRIN will obtain personal identification numbers for all Danish citizens currently treated with LAMAs (all combinations). Recruitment letters will be sent through the official Danish electronic mailbox system (Digital Post). The letter will contain a link to a REDCap questionnaire for the participants to complete if they are interested. The questionnaire will obtain the participant’s personal identification number, select sociodemographic and lifestyle-related variables, confirm current treatment with LAMAs, and obtain consent to participate.

## Assignment of interventions: allocation

### Sequence generation

Patients will be randomized 1:1 to one of the two treatment strategies by computer-generated allocation to either LAMA administration in the morning or evening.

### Concealment mechanism

The concealment mechanism for investigators will be that the database manager and outcome assessors will be blinded. The allocated group will not be concealed from participants.

### Implementation

After providing informed consent, the participant will automatically be provided with a randomization allocation, to either LAMA administration in the evening or the morning, on their screen and sent to their official electronic mailbox, as will the participant be continuously reminded (Table 4).

## Assignment of interventions: blinding

### Who will be blinded

The trial is open-label. Trial participants will not be blinded. The database manager and the outcome assessors will be blinded. Apart from this, all endpoints are assessed using prespecified registry-based definitions to ensure maximal reduction of the risk of bias.

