### Outcomes

The primary efficacy endpoint is the occurrence of hospitalization requiring AECOPD or death from all causes within 12 months. Secondary efficacy endpoints included (i) moderate COPD exacerbations; (ii) all-cause hospitalization; (iii) ICU admission; (iv) need for non-invasive ventilation; (v) all-cause mortality; (vi) SABA use/pick-up rate; and exploratory endpoints (i) relation between adherence and AECOPD hospitalization, (ii) change in CAT score, (iii) change in MRC score, and (iv) change in “soundly sleeping” parameter of CAT.

The details on the primary and secondary outcomes of the study can be seen in Tables 1, 2, and exploratory outcomes in Table 3.

**Table 2 tab2:** Secondary and exploratory endpoint definition.

Endpoint	ICD-10/ATC codes	Inpatient/outpatient/minimum required length of stay/other criteria
Moderate COPD exacerbations	Prednisolone: H02AB06 or Antibiotics: J01CA04, J01AA02, J01CR02, J01MA14	Excluding hospitalizations and emergency room visits: DJ441 (A)
Hospitalization (all-cause)		Inpatient, length of stay ≥24 h
Hospitalization in ICU (all-cause)		Inpatient, ICU, length of stay ≥24 h
Need for NIV	BGDA1	A or B
Mortality (all-cause)		Participant registered as dead in the CPR register.
SABA use/pick-up rate	R03AC02, R03CC02, R03AC03	Danish National Prescription Registry
Change in CAT score	Questionnaire	At 6 and 12 months
Change in MRC score	Questionnaire	At 6 and 12 months

The time frame is ≥1 day after randomization until the end of the study (12 months from randomization) for all outcomes. A = primary discharge diagnosis and B = secondary discharge diagnosis. COPD, chronic obstructive pulmonary disease; ICU, intensive care unit; NIV, non-invasive ventilation; CPR, Central (National) Person Registry; SABA, short-acting beta-2 agonists; CAT, COPD assessment test.

**Table 3 tab3:** Exploratory endpoint definition.

Endpoint	Data source or ICD-10 codes	Inpatient/outpatient/minimum required length of stay/other criteria
Relation between adherence and hospitalization-requiring AECOPD	Questionnaire, DJ440, DJ441	For hospitalizations: Type A diagnosis (primary discharge diagnosis). Inpatient and length of stay ≥24 h, or emergency room visits. Deaths excluded.
Change in CAT score	Questionnaire	At 6 and 12 months
Change in MRC score	Questionnaire	At 6 and 12 months
Change in CAT “soundly sleeping” parameter	Questionnaire	At 6 and 12 months

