## Data collection and management

### Plans for the assessment and collection of outcomes

In addition to what is obtained through the initial questionnaire, all information on baseline characteristics will be collected from Danish nationwide registries. This will be supplemented with data from the initial questionnaire on body mass index, smoking status (including pack-years), FEV1, and asthma. Information on adherence and symptom scores for exploratory outcomes will be obtained through questionnaires. The data from nationwide registries include age, gender, exacerbation history, comorbidities, and relevant medication details. All data used to assess clinical endpoints during the study will be collected from Danish nationwide registries.

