## Statistical methods

### Statistical methods for primary and secondary outcomes

The primary and all secondary outcomes will be analyzed using the intention-to-treat (ITT) approach, which encompasses the entire cohort of randomized participants in the study. Additionally, per-protocol analyses will be conducted for patients taking inhalation medication 6–7 days per week at the allocated administration time for the full duration of the study, along with modified ITT (mITT) analyses for those who have taken less than 6 days or more than 2 days per week for any amount of time. These analyses will be performed on both the primary and all secondary outcomes, providing a comprehensive evaluation of the study’s results.

The primary outcome (hospitalization-requiring AECOPD or death from all causes within 12) will be presented as a fraction with percentage and relative risk with a 95% confidence interval. The groups will be compared using a two-sided binomial test. The same principles will be applied to secondary binomial outcomes. For the SABA pick-up rate, the incidence rate and ratios will be calculated and presented (including 95% confidence intervals) and compared using the chi-squared test. Changes in CAT and MRC (respectively) will be reported as median differences with IQR and compared within and between groups with a paired two-sided Wilcoxon signed-rank test and an unpaired two-sided Wilcoxon rank-sum test. A subgroup analysis will be performed on the primary outcome with the following subgroups: adherence group (high adherence: ≥4–5 days per week of adherence), age (≥65 years), asthma overlap, coexisting heart failure, body mass index (>30 kg/), frequent exacerbator (>1 severe exacerbation within 12 months prior to baseline), and treatment with systemic beta-2 antagonist at baseline. A *p*-value of <0.05 will be considered significant.

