### Methods in analysis to handle protocol non-adherence and any statistical methods to handle missing data

Secondary analyses will include mITT and per-protocol analyses to provide a comprehensive evaluation of the study outcomes. No data on the primary outcome will be missing as national registries will be used for outcome assessment. Only self-reported outcomes such as MRC and CAT can be expected to be missing. It will be assumed all missing data will be missing at random or completely at random to allow for multiple imputations. No imputed data will be presented in the baseline table.

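### The bias safeguard claimed for all endpoints does not cover CAT, MRC and the CAT sleep item, which unblinded participants report themselves

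*Protocol article*

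**What the plan says.** The section on who will be blinded states: "The trial is open-label. Trial participants will not be blinded". It adds that the database manager and the outcome assessors are blinded, and then gives the general assurance: "Apart from this, all endpoints are assessed using prespecified registry-based definitions to ensure maximal reduction of the risk of bias".

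Other sections describe a different source for some outcomes:

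- The section on assessment and collection of outcomes: "Information on adherence and symptom scores for exploratory outcomes will be obtained through questionnaires". Its last sentence says that the data for the clinical endpoints come from the registries, which is narrower than all endpoints.
- Tables 2 and 3 give a questionnaire as the source for change in CAT and change in MRC, and Table 3 does the same for "Change in CAT “soundly sleeping” parameter". All are collected at 6 and 12 months.
- The missing-data section: "Only self-reported outcomes such as MRC and CAT can be expected to be missing".

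The section on statistical methods for primary and secondary outcomes reports CAT and MRC changes as median differences with interquartile range. The arms are compared by "an unpaired two-sided Wilcoxon rank-sum test". That section and the one on additional analyses both set significance at p<0.05. No test is named for the sleep item, so only the general rule reaches it. The Objectives and Outcomes text ranks all three scores as exploratory.

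**The concern.** For a symptom score the participant is the person who rates the outcome. Here the participant knows the arm, so blinding the database manager and the assessors does not protect the rating. A registry definition cannot protect it either, because the score does not come from a registry. The assurance therefore gives these outcomes a property that the design does not provide.

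The two arms also differ in what participants are asked to do. The control arm continues its usual morning inhalation and the evening arm is given a set evening window. A difference in expectation between arms is therefore possible, and sleep is an outcome that participants could easily link to evening dosing. In a trial of this size a small reporting shift can pass p<0.05. A reader who relies on the assurance could then take that result as protected evidence for evening dosing.

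**Working it through.** **The text.** The blinding section says that every endpoint has a registry definition. Tables 2 and 3, the data collection section and the missing-data section say that CAT, MRC and the sleep item are self-reported by questionnaire. These statements cannot all be true. The Methods paragraph of the abstract, read literally, also places the patient-reported assessments among the register data, so the loose wording occurs twice.

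**The plan's own figure.** The only sample size stated is for the primary endpoint: 6,662, or 3,331 per arm. It reproduces:

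- p1 = 16,000/178,000 = 0.0899
- p2 = p1 × (1 − 0.25 × 0.844) = 0.0709
- two-sided alpha 0.05 and power 0.80, pooled variance: 3,226 per arm
- with continuity correction: 3,331 per arm, total 6,662

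No size or power is stated for CAT, MRC or the sleep item.

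**Inputs for the questionnaire outcomes**

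- Randomized: 10,013 (abstract), allocated 1:1, so about 5,006 per arm.
- Questionnaire response: not stated. Assumed range 50% to 100%, that is n of about 2,503 to 5,006 per arm.
- SD of change: not stated. Results are in SD units first, then in points under assumed SDs.

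**Formulas**

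- Observed difference that just reaches p<0.05: 1.96 × √(2/n). A true shift of this size is significant about half the time.
- Shift significant with 80% probability: (1.960 + 0.842) × √(2/n).
- For the planned rank-sum test, divide by √0.955 (its relative efficiency for normal data).

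| Response (assumed) | n per arm | just p<0.05 | 80% probability | 80%, rank-sum |
|---|---|---|---|---|
| 100% | 5,006 | 0.039 SD | 0.056 SD | 0.057 SD |
| 70% | 3,505 | 0.047 SD | 0.067 SD | 0.069 SD |
| 50% | 2,503 | 0.055 SD | 0.079 SD | 0.081 SD |

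A shift of 0.1 SD gives z = 0.1/√(2/n). This is 3.54 at n = 2,500 and 4.74 at n = 4,500, so the shift would be significant in about 94% and 99.7% of trials.

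**In points**

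- CAT, assumed SD of change 5 to 8: the 80% shift runs from 0.056 × 5 = 0.28 to 0.079 × 8 = 0.63 points.
- MRC or sleep item, assumed SD 0.6 to 1.0 grade: from 0.056 × 0.6 = 0.03 to 0.079 × 1.0 = 0.08 grade. That is roughly 3 to 8 net participants per 100 answering one grade better.

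MRC and a single CAT item are coarse scales with many ties, so their figures are approximate.

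**What the planned summary shows.** An interquartile range describes the spread of individual changes, not the uncertainty of the between-arm difference. On a coarse scale both arms can have the same median change while the rank-sum test is significant. The reader would then have a p-value but no usable size or precision for the difference.

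**The case against.** The best defence is that the sentence is loose and the document corrects it elsewhere. The data collection section ties registry sourcing to clinical endpoints, the missing-data section calls CAT and MRC self-reported, and the study-setting section contrasts questionnaire follow-up with endpoints from registries. The trial is openly labelled open-label and the scores are exploratory. All of this stands and keeps the point minor. It does not make the assurance true for these scores.

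A second defence is that any large trial can detect small differences. That is correct. The size matters here only because these outcomes lack the protection claimed for them.

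A reader might infer more than the document supports:

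- *That an expectation effect will make these results significant.* Nothing shows that such an effect exists. Both arms keep their own drug and dose, and a shift of 0.039 to 0.055 SD would be significant only about half the time.
- *That the blinded-assessor statement is false.* The concealment section frames that blinding as applying to investigators and names participants separately. It simply does not reach self-reports.
- *That a missing minimal important difference is a defect.* The plan shown states none, but this is commonly left to an analysis plan or full protocol, and neither is shown.
- *That allocation reminders in the questionnaire months add bias and should be moved.* Participants know their arm from randomization, and Table 4 gives months, not the order of messages. Moving the reminder would gain little.

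**Conclusion.** The contradiction is established from the text alone: the assurance about all endpoints does not hold for change in CAT, change in MRC and the CAT sleep item. The practical consequence is limited to how those three exploratory results may be read. A differential reporting shift of about 0.06 to 0.08 SD would have an 80% chance of being called significant, given 10,013 randomized, an assumed response of 50% to 100%, and either a normal-theory comparison or a rank-sum test on roughly normal changes. The values in points rest further on the assumed SDs.

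A reader might also infer that the trial's main conclusion is at risk. The document does not support that. The primary and registry-based secondary endpoints do have registry definitions, and their intention-to-treat comparisons do not use these scores. Severity is minor.

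**What to change.** 1. In the section on who will be blinded, limit the last sentence to the registry-based endpoints. Add that change in CAT, change in MRC and the CAT sleep item are unblinded, exploratory self-reports. Align the abstract's sentence on patient-reported assessments.
2. In the statistical methods, report each of the three scores as a between-arm estimate with a 95% confidence interval, for example a mean difference in change, or a Hodges-Lehmann shift for CAT. Median and interquartile range can remain as description by arm.
3. State that these results are read by size and precision and are not claimed as significant on p<0.05 alone.

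This needs wording and one extra line of analysis output, with no new data and no change in conduct. The cost is giving up a significance claim on exploratory outcomes. A confidence interval does not remove reporting bias; it only lets the reader see whether a difference is too small to matter.
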